## Abstract

**Rationale:** Treatment of aphasia is still challenging for clinicians and patients. So far, there is proven evidence for “face-to-face” speech therapy. However, the digital age potentially offers new and complementary strategies that may add to treatment outcome in a cost-effective way. Neolexon® is a commercial tablet-based software for treatment of aphasia, which can be applied with the help of a therapist or as self-training by the patient.

**Aims and hypothesis:** In the Lexi study, we aim to determine whether treatment with Neolexon® is superior to standard therapy in acute post-stroke aphasia.

**Sample size estimates:** A sample size of 180 patients, 90 for each group, will be included with an assumed dropout rate of ~20%.

**Methods and design:** Prospective, randomized, parallel group, open-label, blinded-endpoint clinical, and experimental controlled non-invasive trial (PROBE). Adult German native speakers with acute aphasia after stroke are included. Computer-generated, blocked, and stratified randomization by aphasia severity will assign patients to one of two groups: 4 weeks of either standard logopedic speech therapy or logopedic speech therapy with the app version of Neolexon®. Both groups will be instructed in self-training: the frequency and duration of self-training will be documented. Screening for aphasia will be performed using the Language Screening Test (LAST). The severity of aphasia in general and in subitems will be assessed using the Bielefelder Aphasie Screening (BIAS) and the Aphasia Check List (ACL). Follow-up will be assessed after 3 months.

**Study outcomes:** Based on the consensus in our study team, we considered a 10% mean difference in the change of percentile rank (PR) of BIAS to be a minimal and clinically important difference. The primary endpoint is defined as a significant difference in BIAS comparing the two groups. Differences in quality of life, Beck Depression Inventory (BDI), and modified Ranking Scale (mRS) will be evaluated as secondary outcome parameters.

**Discussion:** This trial will determine whether speech therapy with the use of Neolexon® is superior to standard logopedic therapy. Subgroups with the greatest response to Neolexon® will be described. The trial was prospectively registered on the “EU Clinical Trials Register” (NCT04080817)^1^.

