### Selection/Treatment of Subjects

Patients fulfilling the inclusion criteria at screening will be randomized in a ratio of 1:1 into two comparative treatment groups. Patients not capable of giving written informed consent due to physical or mental disorders can be included in the study after written informed consent of the legal guardian. On the other hand, if the inability to give permission is transient, the patient has to acquiesce afterwards.

The procedure considers stratification by aphasia severity to ensure balanced strata, maintaining allocation concealment. The Medical Informatics, Biometry, and Epidemiology (IBE) of the University of Munich will provide an internet-based, password-protected randomization tool “Randoulette^4^,” which chooses the treatment sequence for a new patient who fulfills the eligibility criteria and has signed the informed consent. Randoulette will register the patient by his or her screening number, gender, year of birth, and strata before the allocated number is provided.

Patients will be screened directly after admission to hospital for stroke. The study population includes a broad range of patients with acute aphasia after any stroke (ischemic or hemorrhagic). Inclusion and exclusion criteria are shown in Table 1.

**Table 1 T1:** Inclusion and exclusion criteria for Lexi study.

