Screening for aphasia will be performed using the Language Screening Test (LAST) (25, 26). The LAST is a simple, quick, validated screening instrument focusing on speech comprehension, word repetition, and naming. LAST is conducted using the following parts: “Naming,” “Repetition,” “Automatic speech,” “Picture recognition,” and “Verbal instructions.” A total score of 15 can be achieved, meaning one point per item. The minimum number of points that can be attained is 0 (25, 26). In clinical trials, there is no validation of severity of aphasia using the LAST; however, based on clinical experience and consensus, the severity of aphasia is as follows: 0–5 severe, 6–10 moderate, and 11–14 minimal.

The Aphasia Check List (ACL), developed by Kalbe et al. (27) comprises two main parts: The first part, “Language,” covers a broad range of linguistic aspects, i.e., speaking in series or reading out loud. Communication abilities are evaluated on the basis of a four-level rating scale: From 0 meaning “severe aphasia” to 3 implying lack of disability. Also, writing after dictation is one noteworthy subtest. The second part, “Cognition,” focuses on non-verbal recall using tasks that require logical thinking, attention, and memory. After adding up all subtests, a cutoff score at 135 is defined as aphasia. The ACL takes up to 30 min (27). The ACL is a test that actually allows the severity of aphasia to be quantified. It is known to have test–retest reliability, and it has been used in other studies. However, the ACL does not include all the important speech/language modalities, so the primary endpoint is determined using the Bielefelder Aphasie Screening (BIAS).

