#### Primary Objective

Based on the consensus in our study team, we considered a 10% mean difference in the change of the PR of BIAS to be a minimal and clinically important difference. Our primary objective is to demonstrate a significant improvement of 10% in BIAS comparing the two groups. Differences in quality of life, BDI, and mRS will we evaluated as secondary outcome parameters.

We aimed to recruit 180 participants (90 patients per group), which had 85% power for a 5% two-sided test to address the primary objective. Sample size was adjusted for an assumed dropout rate of ~20%; therefore, at least 144 patients (72 per group) should be analyzed. We expect about 50% of screen fails—based on the calculated sample size, we need to screen 360 patients in our stroke unit.

Data with normal distribution will be presented as mean ± standard deviation (SD), and non-normally distributed data will be presented as median and range (min, max) or interquartile range (IQR). For categorical variables, counts and percentages will be given. Data will be compared with the chi-square test, Mann–Whitney test, or Student's *t*-test where appropriate. A two-sided *p*-value of <0.05 will be considered statistically significant. Binary logistic regression models will be used to analyze the association between study group and outcome parameters. Results will be adjusted for well-known outcome predictors after stroke, e.g., age, sex, NIHSS, pmRS, lesion size, treatment, comorbidities, and complications. Statistical analysis will be performed with the Statistical Package for the Social Sciences, SPSS (SPSS Inc., 21.0 for Windows).

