One of the potential limitations of our work is that only patients with post-stroke aphasia are included. There will be no conclusive data from aphasia after other causes. In addition, we decided not to investigate chronic aphasia. However, we are considering the possibility of performing further trials on these topics. Non-fluent German speakers and severely affected patients who are unable to use the tablet-based app due to the fact that physical or mental conditions are excluded, as are patients with a reduced life expectancy. Due to the lack of previous studies, we cannot conduct a sample size calculation based on treatment effects. Thus, this study could be underpowered to show an effect in the interventional group.

Our goal is to show whether patients could benefit from Neolexon® computer-based speech therapy. Further studies might be necessary to approach the main problem of other aspects of aphasia. Other important factors that could be interesting to analyze are motivation for speech therapy, reducing negative affective symptoms during treatment, and lower workload for other family members (43).

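### The abstract makes a subgroup's own observed response the reason for reporting it, which overstates the effect in the subgroup reported

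*Protocol article*

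**What the plan says.** The Discussion paragraph of the abstract states: "Subgroups with the greatest response to Neolexon® will be described". This is the article's only mention of subgroups. The Primary Objective section, which carries the statistical methods, describes comparisons between the two groups and adjusted regression, and does not qualify the abstract's sentence.

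Two other places bear on the point. Under Selection/Treatment of Subjects, randomisation is stratified: "The procedure considers stratification by aphasia severity to ensure balanced strata". The description of LAST under Interventional Methods gives severity bands, "0–5 severe, 6–10 moderate, and 11–14 minimal", but does not say that these bands are the randomisation strata.

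The yardstick for size is in the Primary Objective section: "we considered a 10% mean difference in the change of the PR of BIAS to be a minimal and clinically important difference".

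**The concern.** The sentence states a criterion: a subgroup is described because its response is the greatest. That is selection on the outcome. The largest of several estimates tends to be the one that chance has pushed up most, so its expected value exceeds the true effect. If the true effect is uniform, the subgroup on top is there by chance alone. Calling the result descriptive avoids a formal test but does not remove this bias.

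The wording is also open on what response means. If it means the between-group difference within a subgroup, the problem is the selection bias just described. If it means improvement among patients using the app, a further problem arises. Patients are enrolled in the acute phase, and the article's own Discussion says that prognosis depends on initial severity. Ranking subgroups by improvement within one arm would then partly rank them by how much they recover regardless of the app.

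At stake is the credibility of any subgroup statement in the final report, particularly if the overall result is null or borderline.

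**Working it through.** **Inputs from the article**
- Difference of interest: 10, read here as percentile-rank points of BIAS (Primary Objective).
- Design: "randomized in a ratio of 1:1 into two comparative treatment groups" (Selection/Treatment of Subjects).
- 72 per group analysed, 90 per group recruited, about 20% dropout (Primary Objective).
- Test and power: "which had 85% power for a 5% two-sided test to address the primary objective".

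**Inputs that are assumptions**
- SD of the change in BIAS: not given. The article's Discussion says: "Due to the lack of previous studies, we cannot conduct a sample size calculation based on treatment effects". The value used below is back-solved, and a range is shown.
- Number and size of subgroups: not given. Three equal strata are used for illustration, so 72/3 = 24 per arm in each.

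**Step 1. Reproduce the plan's own figure.** 72/(1 − 0.20) = 90 per group and 144/(1 − 0.20) = 180. Both match.

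**Step 2. SD implied by the power statement.** SD = 10 / [(1.960 + 1.036) × √(2/72)] = 10 / (2.996 × 0.1667) = 20.0. With SD 20, 72 per group gives 85.1% power.

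**Step 3. Best of three strata, no true effect.**
- Standard error of the difference in one stratum: 20 × √(2/24) = 5.77.
- Expected maximum of three independent standard normal values: 0.846.
- Expected best-stratum difference: 0.846 × 5.77 = 4.9 points, about half of the 10-point important difference.
- Chance that the best stratum shows 10 or more: 1 − Φ(10/5.77)³ = 1 − 0.958³ = 0.12. Simulation gave a mean of 4.88 and a probability of 0.118.

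**Step 4. Sensitivity to the SD.**
- SD 15: standard error 4.33; mean 0.846 × 4.33 = 3.7; chance of 10 or more 1 − Φ(2.31)³ = 3%.
- SD 25: standard error 7.22; mean 0.846 × 7.22 = 6.1; chance of 10 or more 1 − Φ(1.39)³ = 23%.

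**Step 5. Sensitivity to the subgroup structure (simulation, SD 20, no true effect).** With 3, 5 or 8 two-level factors, giving 6, 10 or 16 overlapping half-sample subgroups, the best subgroup averages +4.5, +5.3 or +6.1 points. It reaches 10 points in 8%, 11% or 15% of trials.

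**Step 6. Uniform true effect of 10.** The best of three strata is expected to show 10 + 4.9 = 14.9 points, an overstatement of about 49%, although no stratum differs from another.

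**Step 7. What an interaction test can do.** For two half-samples (36 per arm each, SD 20), the standard error of the difference between subgroup effects is 20 × √(2/36) × √2 = 6.67. Power for a 10-point difference is Φ(10/6.67 − 1.96) = Φ(−0.46) = 32%.

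**The case against.** The strongest reply is that one summary sentence in an abstract is being read as an analysis rule. Describing which subgroups respond most is compatible with a prespecified set of subgroups, all displayed and tested for interaction. A full protocol or analysis plan that is not shown may contain exactly that. Much of this stands:

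- A reader might infer that effects will not be compared between subgroups. The article does not say so; it is silent.
- The lack of a subgroup list, multiplicity rule or interaction test in a journal article is not a fault, and the point does not rest on it.
- A reader might infer from the abstract that identifying responders is one of two main deliverables and will guide whom to treat. The body does not support this. The objective there is the BIAS comparison, with quality of life, BDI and mRS as secondary outcomes, and subgroups are not mentioned.
- A reader might conclude that such responder groups are often spurious. No single figure supports that. The frequency depends on the SD and on the number of subgroups, and neither is given.
- The LAST bands cannot be taken to be the randomisation strata. Three equal strata are an assumption.
- If response means change within the app arm, the between-arm arithmetic above does not apply, although the difficulty is then greater.

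What the reply does not remove is the criterion itself. The sentence selects on observed response and nothing in the article qualifies it. If a fuller plan reports every prespecified subgroup, the published sentence misdescribes that plan and still needs correcting.

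**Conclusion.** The concern holds in a limited form. Followed as worded, the sentence gives an upward-biased effect in whichever subgroup is reported. Under SD 20, three equal strata and no true effect, the bias is about 4.9 points, and a 10-point result appears in about 12% of trials. For SD 15 to 25 the bias is about 3.7 to 6.1 points. That the bias is upward follows from the selection itself; the size is illustrative, because the SD and the subgroup structure are assumed. The primary comparison, its significance level and the sample size are not affected. This is a minor-to-moderate point about wording and reporting, and it does not call the main result into question.

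**What to change.** Replace the sentence with text such as:

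> The between-group difference in change in BIAS will be shown with 95% CI in every aphasia-severity stratum used for randomisation, with a treatment-by-severity interaction test. Any other subgroups examined are exploratory and all will be shown. No subgroup will be singled out as responding on the basis of its own observed effect.

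This also settles that response means a between-group difference. The cost is one sentence and one interaction term, and it uses the stratification already planned. There are two downsides. The interaction test has low power (about 32% in the case worked above), so the gain is unbiased reporting rather than a firm answer on who responds. The subgroup statement will also look less favourable than a report of the best subgroup alone.

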## Introduction

Aphasia as a neuropsychological language disability is a condition affecting communication, cognition, and identity negatively (1). Therefore, aphasic syndromes are connected to affective disorders like depression (2) or fatigue and are associated with a negative impact on quality of life. The latter is particularly important with regard to the advantages of the self-therapy (3–5). The incidence of aphasia is 43/100,000, and it is a first and leading symptom in a significant proportion of stroke patients (6, 7). In Germany, it is assumed that about 70,000 people suffer from aphasia (8). Aphasic syndromes are frequently seen in stroke caused by lesions of the dominant hemisphere (3); however, they can also be caused by trauma, epilepsy, or degenerative diseases (9). The effect of “standard” speech therapy in patients with aphasia is already scientifically proven (10–12). Regarding the therapy of aphasia, intensified logopedic standard therapy more than 5 h per week was shown to be effective (10, 13). Moreover, intensive speech therapy for 3 weeks (more than 10 h/week) was suggested to improve communication skills significantly (11). In addition, communication-based treatment as well as logopedic group therapy were shown to have a positive effect as well (13, 14) Early treatment and high intensity are potentially effective (13), especially in stroke patients (15), but it should be noted that not every high-intensity therapy is applicable to all patients. Further, results regarding very early rehabilitation after stroke are lacking (15). The German Neurology Society, therefore, underlines the urgency of immediate treatment. Furthermore, 5–10 h per week should be applied to show a significant benefit (16). However, it can be difficult to meet these demands in clinical practice.

Software-based treatment and the use of modern devices can offer a potential and modern addendum to face-to-face speech-language therapy of aphasic patients. In the digital age and its applications on tablets and smartphones, it is important to investigate modern treatment options especially in the neurologic field. A small population study investigating the effect of computer-assisted self-training vs. nonlinguistic cognitive therapy in 18 patients showed improved communication skills (17, 18). Due to different limitations concerning the population, further investigations are necessary in the future (19). A fundamental study in this field was the “BIG CACTUS” trial: 240 patients with post-stroke aphasia improved in word finding after computer-based treatment, although there was no enhancement seen in conversation skills. In this trial, both groups with post-stroke aphasia received the usual care, but the study group was additionally treated with computerized self-therapy. However, this trial was a power analysis regarding chronic aphasia (20). Another notable study researching the outcome of electrical brain stimulation on post-stroke aphasia demonstrated effectiveness in 26 patients (21).

Neolexon® is a tablet-based application offering tailored training lessons for patients with aphasia. Neolexon® was developed by two speech therapists [name] and [name] and programmed by IT experts from the Ludwig Maximilians University (LMU) Munich. It is certified as a health care product^2^ In this study, we seek to determine whether a standard logopedic therapy is less effective than a tablet-based speech therapy with Neolexon® in post-stroke aphasic patients. The aim is to prove the effectiveness of digital applications on aphasia after (ischemic or hemorrhagic) stroke.

## Methods and Analysis

### Design

The Lexi Study is a prospective, randomized, open-label, clinical, and experimental controlled noninvasive trial with two groups. Clinical follow-up will be obtained during an outpatient clinic visit within an endpoint-blinded design. The trial was approved by the ethics committee of the LMU, Munich, Germany (project number 19-068). The trial was prospectively registered on the “EU Clinical Trials Register” (NCT04080817)^1^.

The Neolexon® App is an individualized software that can be used together with a speech therapist (therapist app version) or alone (self-training app) at home. Any user can compile training sessions from up to 8,000 words and 1,200 sentences and sort them into different categories. Pictures, which are also used in standard speech therapy are also digitally established in Neolexon®. The speech therapist generates an individual profile of the patient and can adjust the number of syllables, syllable structure, word accent, and word frequency. Words can then be searched by category, for example, “food,” and pictures can be displayed that the patient has to name. Neolexon® is intended for auditory speech comprehension, oral and written naming, and reading comprehension training. During self-training, the patient can then log in by clicking on the “patient” button and continue training with his adjusted profile without restriction. The application detects therapy success automatically and offers continuous adjustment during the exercise. In addition, the application systematically records the duration of all training lessons^3^

### Selection/Treatment of Subjects

Patients fulfilling the inclusion criteria at screening will be randomized in a ratio of 1:1 into two comparative treatment groups. Patients not capable of giving written informed consent due to physical or mental disorders can be included in the study after written informed consent of the legal guardian. On the other hand, if the inability to give permission is transient, the patient has to acquiesce afterwards.

The procedure considers stratification by aphasia severity to ensure balanced strata, maintaining allocation concealment. The Medical Informatics, Biometry, and Epidemiology (IBE) of the University of Munich will provide an internet-based, password-protected randomization tool “Randoulette^4^,” which chooses the treatment sequence for a new patient who fulfills the eligibility criteria and has signed the informed consent. Randoulette will register the patient by his or her screening number, gender, year of birth, and strata before the allocated number is provided.

Patients will be screened directly after admission to hospital for stroke. The study population includes a broad range of patients with acute aphasia after any stroke (ischemic or hemorrhagic). Inclusion and exclusion criteria are shown in Table 1.

**Table 1 T1:** Inclusion and exclusion criteria for Lexi study.

**Inclusion criteria**
≥18 years of age
German mother tongue
Acute aphasia after stroke
Life expectancy > 1 year
Written informed consent
**Exclusion criteria**
<18 years of age
Non-native German speaker
Other causes of aphasia
Life expectancy <1 year
Informed consent missing
Impossible to use tablet-based app due to physical or mental conditions

### Interventional Methods

Patients will be screened and assessed for eligibility directly after admission to our stroke unit. Patients eligible for entry to the study will be randomized and assigned to one of the two treatment arms after written informed consent. Each group (standard speech therapy vs. speech therapy with the therapist app version of Neolexon® therapy) should have a minimum of 50 participants. Because of the dropout rate of ~20%, at least 70 patients should be included in each group.

Each study arm (treatment group and control group) with a duration of 4 weeks includes three study visits. Follow-up will be assessed after 3 months (study visit 4). Figure 1 shows the study scheme and Table 2 demonstrates the schedule of enrollment and assessment as well as interventions at each study visit during the Lexi study.

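### The protocol gives two conflicting per-group minimums for the same 20% dropout (50 and 70 versus 72 and 90), and the lower pair would not carry the stated 85% power

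*Protocol article*

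**What the plan says.** Three places in the protocol article give a sample size, all in current text.

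- **Interventional Methods:** each group "should have a minimum of 50 participants", followed by "Because of the dropout rate of ~20%, at least 70 patients should be included in each group".
- **Abstract, sample size estimates:** "A sample size of 180 patients, 90 for each group, will be included with an assumed dropout rate of ~20" percent.
- **Primary Objective:** the recruitment aim is 180 (90 per group), "which had 85% power for a 5% two-sided test to address the primary objective". It continues: "Sample size was adjusted for an assumed dropout rate of ~20%; therefore, at least 144 patients (72 per group) should be analyzed". The same paragraph expects about half of those screened to fail and so plans to screen 360.

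The effect of interest is also in Primary Objective: "we considered a 10% mean difference in the change of the PR of BIAS to be a minimal and clinically important difference". Allocation is 1:1 (Selection/Treatment of Subjects). No SD for the change in percentile rank appears anywhere, and the Discussion says: "Due to the lack of previous studies, we cannot conduct a sample size calculation based on treatment effects".

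**The concern.** The same dropout rate is used to justify two different inclusion figures, 70 and 90 per group, and two different lower limits, 50 and 72. A minimum tells the team when the trial is large enough, so two minimums give two answers. A trial that meets the figures in Interventional Methods can fail the requirement in Primary Objective.

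What is at stake is the power statement. The 85% is attached only to the larger set of figures. If recruitment fell short and the team judged the result adequate by the lower figures, the type II error would be well above the 15% that the protocol reports, and a null result would be harder to interpret.

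**Working it through.** **Inputs.** From the article: two-sided 5% test, 85% power, 10-point difference in change of BIAS percentile rank, 1:1 allocation, dropout about 20%, and the pairs 50 and 70 and 72 and 90 per group. Not in the article: the SD. It is back-solved below from the 85% claim and is an assumption.

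**Step 1. Reproduce the larger pair.** Included = analysed / (1 − dropout).
- 72 / 0.8 = 90 per group, and 144 / 0.8 = 180 in total. Both agree with Abstract and Primary Objective.
- Screening: 180 / 0.5 = 360. This also agrees.

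**Step 2. Try the smaller pair.** Interventional Methods says participants and does not say whether 50 is before or after dropout. Because the next sentence raises the number for dropout, 50 is taken here as the number remaining.
- 50 / 0.8 = 62.5, so 63. The cruder 50 × 1.2 gives 60. Neither is 70.
- Backwards: 70 × 0.8 = 56, not 50.
- Loss needed to go from 70 to 50: 1 − 50/70 = 28.6%, not about 20%.

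**Step 3. Compare the minimums.**

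| | Included per group | Left after 20% loss | Stated minimum |
|---|---|---|---|
| Interventional Methods | 70 | 56 | 50 |
| Primary Objective | 90 | 72 | 72 analysed |

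The shortfall is 72 − 56 = 16 per group. With no loss at all, 70 is still below 72.

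**Step 4. Power at the smaller sizes.** For two means, n per group = 2(z₀.₉₇₅ + z₀.₈₅)² SD² / δ², with z₀.₉₇₅ + z₀.₈₅ = 1.960 + 1.036 = 2.996. Solving for the SD with δ = 10:
- If the 85% belongs to 72 analysed: SD = 10 / (2.996 × √(2/72)) = 20.0.
- If it belongs to 90 per group: SD = 10 / (2.996 × √(2/90)) = 22.4.

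Power at n per group is Φ(10 / (SD × √(2/n)) − 1.960). For n = 56 and SD 20.0 this is Φ(2.643 − 1.960) = Φ(0.683) = 75.3%. The t columns use a noncentral t-test, with the effect size again set so that the reference size gives exactly 85%.

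| n per group | 85% at 72: normal | 85% at 72: t | 85% at 90: normal | 85% at 90: t |
|---|---|---|---|---|
| 50 | 70.4% | 70.2% | 60.8% | 60.4% |
| 56 | 75.3% | 75.1% | 65.7% | 65.4% |
| 70 | 84.0% | 84.0% | 75.3% | 75.1% |
| 72 | 85.0% | 85.0% | 76.4% | 76.3% |

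Within each reading the figures do not depend on a chosen SD, because the 85% fixes the ratio of difference to SD.

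**The case against.** **The lower figures are floors.** Recruiting 90 per group satisfies every sentence at once, so the two sets do not strictly exclude each other for recruitment. That stands. The conflict is between the lower bounds, and it remains: meeting 70 included does not meet 72 analysed.

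**The slip from 50 to 70 is on the safe side.** Sixty-three would suffice to keep 50 at 20% loss, and 70 exceeds that. This also stands. The figure is loosely derived, but it does not endanger the 50. Reading 50 as the number after dropout is an inference. If 50 were instead the number included, the gap to 90 would be wider.

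**The governing target is clear.** Abstract, power statement and screening figure all point to 180, and only Interventional Methods differs. This is a good reason to expect the correction to go that way. It does not remove the contradiction.

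**The 85% is itself weakly grounded.** The Discussion disclaims a calculation based on treatment effects and warns that the study may be underpowered. For that reason the loss is given only relative to the 85%, and for both readings of which sample size the 85% describes. The sentence literally attaches it to 180 recruited, while the dropout adjustment that follows suggests 144 analysed.

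**Stronger readings to avoid.** A reader might infer that the trial is allowed to stop at 70 per group, or that two end points for recruitment in an open-label trial would inflate the type I error. The article does not support either. It states no stopping point at 50 or 70 and plans no interim test. The staff access to the database described under Data Analysis is for maintaining the data. An inconsistent minimum is not a second analysis.

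**Conclusion.** The point holds as an inconsistency in a figure the trial relies on. The article has two sets of minimums for the same dropout rate. Only the pair of 72 analysed and 90 included is arithmetically coherent and connected to a power statement. The 50 and 70 pair implies a 28.6% loss where about 20% is stated, and 70 included would leave 16 per group fewer than the 72 required.

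A trial that met only the lower figures would have about 70% to 75% power if the 85% refers to 72 analysed, or about 60% to 65% if it refers to 90. In each range the lower value is for 50 per group and the higher for 56. The type II error would then be about 25% to 40% in place of 15%. These figures assume a two-sample comparison of means, a 10-point difference, and an SD implied by the 85% claim (about 20 or about 22), since the article gives none.

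The conclusion does not extend to early stopping or to type I error.

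**What to change.** Delete or correct the two sentences in Interventional Methods that give 50 and 70 per group, so that this section, the Abstract and Primary Objective state one target: 180 randomised (90 per group), with at least 144 analysed (72 per group). It would help to say in the same place whether the 85% power refers to the 144 analysed or the 180 recruited.

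If 70 per group is the real target, the Abstract and Primary Objective must change instead. They would give 140 randomised, about 112 expected to be analysed (56 per group) and, at 50% screen failure, 140 / 0.5 = 280 screened. The 85% would be replaced by the power for about 56 per group, with the assumed SD stated and justified.

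Either way this is a change of wording. The first option needs no patients beyond the 180 already stated.
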